The aim of our study is to explore the implementation of physical activity policies based on the WHO’s recommendation of a whole-school approach and to examine associations between a derived active environment score and children’s physical activity, mental health and educational performance.

Our aim is underpinned by the following research questions:

Which of the WHO’s policies and practices are currently implemented by primary schools in Greater London to create a physically active school environment?Do schools with a higher active school environment score have better physical activity, mental health and educational performance among their pupils?How equitable is the level of an active school environment across subgroups of children including those living in deprived areas, minority ethnic groups and those with disabilities?

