### Sample size

The power calculation for this study used a multi-level model to account for the hierarchical structure of the data, with pupils (level 1) nested within schools (level 2). The model included random intercepts to capture variability between schools and examined the relationship between Active Environment Score (maximum score 50 points) and school day physical activity (in min). The analysis adjusted for key covariates such as sex (with females expected to engage in fewer than 10 min of physical activity), ethnicity, weekend physical activity, bioimpedance (used as a proxy for body composition), area deprivation and month of assessment (with higher activity expected during warmer months).

Based on the data collected to date, the sample size analysis included 600 pupils from 20 schools, with an average of 30 pupils recruited per school. The sample size of 600 pupils was the minimum number required for our power calculations; however, we aimed to recruit 1000 children to account for potential data losses (i.e., lost accelerometers, incomplete questionnaires, etc). 17 schools had preobserved Active Environment Scores ranging from 26 to 41, while the scores for the remaining three schools were simulated within this range for consistency.

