### Statistical analysis

All data collection for the study has been completed. The data are being processed and cleaned in preparation for the analysis. We will characterise features of our study population including child sex, ethnicity and adiposity. We will report characteristics of schools including school size, ethnic mix, Ofsted rating, percentage eligible for free school meals and area-based deprivation. We will present school and pupil level baseline characteristics by active environment scores with summary measures (totals, percentages, means and SD, medians and IQRs as appropriate).

The main analysis will treat the main outcome (physical activity during the school day) as a continuous variable. Decisions on valid accelerometer data to include in the analysis will be made when reviewing the data. We will use mixed-effects regression models to estimate the association between physical activity acceleration and the active school environment score. We will include pupil-level covariates (sex, ethnicity) and account for clustering at the school level by including random effects. Covariates will be included in the model in stages to assess how much each contributes to diluting or increasing the effect. To measure equity, the primary analysis will adjust for pre-specified school characteristics including school size, pupils eligible for free school meals, pupils whose first language is not English, children with Special Educational Needs and Disabilities and area-level deprivation. Sensitivity analysis will include clustering at the class-level within the school.

Results will be reported with a 95% CI. Mixed effects regression models as described for physical activity will be repeated for the outcomes of mental health and educational performance. All analyses will be carried out using Stata v18.5 and R statistical software. We will report our findings in line with the Strengthening the Reporting of Observational Studies in Epidemiology^33^ and Logical Explanations & Visualizations of Estimates in Linear mixed models guidelines^34^ for reporting cross-sectional studies.

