## Discussion

Schools play a critical role in helping embed the importance of PA by promoting active health behaviours, increasing opportunities for children to be physically active and creating active environments that encourage children to be physically active throughout the school day.^4 35 36^

The HAPPY study will be the most comprehensive exploration to date of how whole-school physical activity practices and policies are implemented in real-world settings according to the WHO key domains, whether promoting active environments is associated with children’s increased physical activity, improved mental health and educational performance and whether opportunities to be physically active are available equitably.

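### The step labelled as measuring equity has physical activity as its outcome, so it does not estimate how the Active Environment Score differs across subgroups (research question 3)

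*Protocol article*

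**What the plan says.** The third research question, in the Introduction, asks "How equitable is the level of an active school environment across subgroups of children including those living in deprived areas", and goes on to name minority ethnic groups and children with disabilities. The Discussion repeats the aim as finding out "whether opportunities to be physically active are available equitably".

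The Statistical analysis section makes four statements that bear on this:

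- The model: "We will use mixed-effects regression models to estimate the association between physical activity acceleration and the active school environment score".
- Its pupil-level terms: "We will include pupil-level covariates (sex, ethnicity) and account for clustering at the school level by including random effects".
- The equity step: "To measure equity, the primary analysis will adjust for pre-specified school characteristics including school size, pupils eligible for free school meals". The list continues with first language other than English, SEND and area-level deprivation.
- A descriptive table: "We will present school and pupil level baseline characteristics by active environment scores with summary measures". The characteristics listed for reporting are child sex, ethnicity and adiposity, and school size, ethnic mix, Ofsted rating, free-school-meal eligibility and area deprivation.

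The section states no model with the score as outcome, no interaction and no stratified estimate.

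**The concern.** The research question is about the level of the school environment, so the quantity wanted is a difference in the Active Environment Score between subgroups. The only analysis given the purpose of measuring equity puts the score on the other side of the equation, as the exposure for pupil activity, and enters the subgroup variables as adjusters. The purpose and the method in that one sentence do not match.

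This is not a detail that a condensed article leaves to an analysis plan. The article names a purpose and attaches a method to it, and an analysis plan that followed the sentence faithfully would carry the mismatch forward. At stake is the answer to one of three research questions, in a study meant to feed policy briefings and to inform work on inequalities. An adjusted association offered as the equity result would leave the provision question without an estimate.

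**Working it through.** The plan states no figure for equity, so there is none to reproduce. Its power figure (81% at 0.55 min per score unit, 600 pupils in 20 schools) concerns the score–activity slope only. The check is therefore on what each model estimates.

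**Step 1. The estimand of research question 3.** Let A be the Active Environment Score and D a subgroup variable such as area deprivation. Equity of level is the coefficient g in

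A = g0 + g·D + error.

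**Step 2. The estimand of the stated equity step.** With Y as physical activity, the stated model is

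Y = a + b·A + c·D + school effect + error.

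Here b is the change in activity per score unit at fixed D, and c is the difference in activity per unit of D at fixed score. Neither b nor c is a function of g. Changing how A is distributed over D changes the precision of b and c, not what they estimate.

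**Step 3. Numerical illustration.** All values are assumed, because the article gives no deprivation effect and no residual SD. There are 20 schools and 4,000 replicates. Mean score is 33.5, the midpoint of the 26–41 range in the Sample size section. Score SD is 4.3, close to 15/√12 = 4.33 for a uniform spread over that range. True b is 0.55 min per unit, true c is −2 min per SD of deprivation, and the residual SD of school means is 3.5 min. School means were fitted by least squares.

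| Average score gap per SD of deprivation (points) | Estimated b | Estimated c |
|---|---|---|
| 0.01 (even provision) | 0.55 | −1.99 |
| −2.14 (deprived schools score lower) | 0.55 | −2.00 |
| +2.13 (deprived schools score higher) | 0.55 | −2.00 |

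The adjusted model gives the same average answer in all three cases. The invariance follows from step 2 and does not depend on the chosen values.

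**Step 4. Does staged entry help?** The plan also says "Covariates will be included in the model in stages to assess how much each contributes to diluting or increasing the effect". In least squares, the shift in the score coefficient when D is added is

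b(unadjusted) − b(adjusted) = c·δ,

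where δ is the slope of D on A. In the second row of the table the assumed correlation is −0.5, so δ = −0.5/4.3 = −0.116 and the shift is (−2)(−0.116) = 0.23, from 0.78 to 0.55. The shift is a product of two relations. If c were 0 the shift would be 0 however large the score gap. Staged entry therefore does not isolate provision.

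**Step 5. What the descriptive table covers.**

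| Subgroup in research question 3 | Among characteristics listed for reporting? | Estimated gap with CI stated? |
|---|---|---|
| Deprived areas | Yes (area deprivation, free school meals) | No |
| Minority ethnic groups | Yes (child ethnicity, school ethnic mix) | No |
| Children with disabilities | No (SEND appears only as an adjuster) | No |

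The table addresses two of the three subgroups, with summary measures only.

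**The case against.** The strongest reply is that research question 3 is descriptive and the plan already tabulates characteristics by score in the same section. A question about level does not demand an adjusted model, and a condensed article may leave secondary models to an analysis plan. Much of this stands. A reader might infer that research question 3 cannot be answered at all from the stated analyses. The documents do not support that, because the table gives a partial answer for deprivation and ethnicity. What remains is that the sentence naming equity as its purpose points to a different model, and that disability is missing from the characteristics listed for the table.

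Three other strong readings also fail:

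- That adjustment removes the subgroup differences. It does not: the covariate coefficients are still estimated, but they describe activity at a given score. The fault is the choice of outcome.
- That a small covariate coefficient will be reported as evidence of equity. The article nowhere says so. What size that coefficient takes depends on assumptions about the direct effect of deprivation on activity that the documents do not supply.
- That research question 3 also asks whether the score–activity slope differs between subgroups. Its wording, and that of the Discussion, concerns level and availability, so subgroup slopes are a further question.

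The absence of school ethnic mix from the adjustment list is not an error either. The list is introduced as non-exhaustive, and pupil ethnicity is in the model.

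**Conclusion.** The equity sentence is wrong as written. Covariate adjustment of a physical-activity model does not estimate how the Active Environment Score is distributed across deprived areas, ethnic groups or children with disabilities. This rests on the stated roles of outcome and exposure, not on the simulated values.

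The consequence is limited to research question 3, one of three. The covariates remain reasonable confounders for research question 2, whose primary analysis is unaffected, and no new data are needed. It should be fixed. The article says the data are still being processed and cleaned before analysis, so the correction can still be prespecified.

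**What to change.** 1. Delete the opening three words of the adjustment sentence, and describe those covariates as confounders for research question 2.
2. For research question 3, across all schools returning the survey, analyse the Active Environment Score as the outcome by area deprivation, percentage eligible for free school meals, ethnic mix, percentage whose first language is not English, and percentage with SEND. Report differences with 95% CIs.
3. Add SEND to the characteristics tabulated by score.
4. Score-by-subgroup interactions in the pupil study are optional and go beyond research question 3. If added, label them exploratory: the power calculation covers only the main effect, and "the sample size analysis included 600 pupils from 20 schools, with an average of 30 pupils recruited per school".

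The cost is wording and a few extra models on data already collected, assuming the school characteristics can be attached to every responding survey school. The survey went to 1,826 schools, so it is the natural dataset for this question, although the article does not give the number returned and itself notes that low response may limit generalisability. The results will describe schools by their composition rather than individual children, and should be worded that way.

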## Ethics and dissemination

Ethical approval has been received by Imperial College London Research Ethics Committee (reference: 6800895). All data collected have been pseudoanonymised (to allow for the removal of data for any participant withdrawing after data have been collected) and held at Imperial College London on secure servers and encrypted with access limited to the study team only. Ethical approval for this research study was granted on the basis that the data were stored securely and only accessible to the research team; therefore, the data will not be uploaded or shared via a repository. However, requests for access to deidentified data may be directed to the principal investigator (SS) who is responsible for data integrity and management.

The findings of this study will be disseminated through scientific peer-reviewed journals, national and international conference presentations, policy briefings and a summary of findings (eg, report, infographic) will be shared with the participating schools.

## Discussion

Schools play a critical role in helping embed the importance of PA by promoting active health behaviours, increasing opportunities for children to be physically active and creating active environments that encourage children to be physically active throughout the school day.^4 35 36^

The HAPPY study will be the most comprehensive exploration to date of how whole-school physical activity practices and policies are implemented in real-world settings according to the WHO key domains, whether promoting active environments is associated with children’s increased physical activity, improved mental health and educational performance and whether opportunities to be physically active are available equitably.

### Potential strengths and limitations

A key strength of the HAPPY study is that it is conducted in a diverse, multiethnic urban conurbation which will identify whether physical activity promotion and equitability differ across Greater London boroughs with different levels of deprivation. Findings will therefore potentially be representative of other diverse urban conurbations. A further strength is accelerometer assessed physical activity which will provide more accurate estimates of daily physical activity minimising the recall bias of participant self-report methods that typically lead to overestimates of physical activity.^37^ Furthermore, accelerometers worn on the non-dominant wrist and processing the raw accelerometer data in 5 s epochs will reduce effects of short intermittent outbursts (eg, random arm movements) included in the average acceleration values when calculating time spent in different PA intensities. This provides a more accurate measure of total PA. Potential limitations of the study include the cross-sectional design of the study; we will only be able to assess associations rather than cause and/or effect. Additionally, schools may not be representative of all schools in Greater London.

Global policies are focused on reducing physical inactivity by 15% by 2030,^2^ where inequalities may be best addressed during childhood when healthy behaviours can be embedded. The results of our study will therefore be of interest to public health policymakers, teachers, parents and children. The findings from the HAPPY study will determine how physically active school environments are associated with children’s physical activity, mental health and educational performance. This study has the potential to inform national strategies for the promotion of physical activity in schools, targeting all children and contributing towards reducing physical activity inequalities in child health.
